#### Allowance for participant attrition

On the basis of historical data from similar gastrointestinal RCTs (23) and our pilot study (attrition rate: 6.25%), we anticipate a 10% attrition rate in the full-scale trial (due to factors such as loss to follow-up, adverse events, or withdrawal of consent). To account for this, we inflated the sample size by 10%. The final sample size per group was calculated as follows: 47 patients (base size) ÷ (1–0.10 attrition rate) ≈ 52 patients.

To simplify randomization and ensure balance between groups, we rounded this number to 50 patients per group, resulting in a total sample size of 100 patients for the study.

### Recruitment

To ensure timely enrollment of the target 100 patients (50 per group) and maintain adherence to the study timeline, a multifaceted, patient-centric recruitment strategy has been designed. This strategy integrates clinical collaboration, targeted outreach, streamlined screening processes, and retention-focused support—all aligned with the study’s inclusion/exclusion criteria (e.g., adults aged 18–70 years with ultrasound-confirmed small gallbladder stones, no prior cholecystectomy, and the ability to complete the 30-day follow-up).

### Allocation

Eligible candidates will be identified through a systematic medical record review and approached for participation via proxy contact. Study randomization will be managed by biostatisticians using a validated computer algorithm to generate a 1:1 allocation sequence, with 100 sequentially numbered sealed opaque envelopes independently encoded and securely stored in a tamper-evident repository.

After confirming that the inclusion criteria have been satisfied, two designated researchers will verify the patient’s identity. They will record the number of unopened envelopes before simultaneously opening the allocation document and signing it together. The trial nurse will administer the corresponding oral treatment protocol to the patient in accordance with their allocation number.

Both the functional fatty acids and the placebo were manufactured by (Seawit) Qingdao Life Science Co., Ltd., China.

Treatment assignments will be securely transmitted by an independent study team. Attending physicians will receive unique assignments for each patient only after all the preintervention protocols have been completed. These protocols include a comprehensive clinical evaluation, the collection of signed informed consent documents, and the confirmation of procedural readiness by the study team.

### Blinding

Both participants and all study personnel involved in intervention administration, clinical assessment, ultrasound examination, and data collection will be blinded to group assignments (double-blinding). The statistician conducting the final data analysis will also remain unaware of group allocations throughout the analysis process. Unblinding will be permitted only after all data have been collected and locked for final statistical analysis.

### Data collection and management

All the data are prospectively collected and managed by well-trained research volunteers.

Baseline data, including age, sex, body mass index (BMI), small gallbladder stone content, gallbladder volume, gallbladder wall thickness, serum bilirubin, the numerical rating scale (NRS) score, postintervention diarrhea, nausea, vomiting, pancreatitis, gastrointestinal bleeding, and other complications, will be collected. This will reflect the characteristics of the participants.

Data, including the expulsion rate of small gallbladder stones and whether there are complications, will be collected each day, starting from 1 day before the intervention to 1 month after the intervention.

Undetected results should have the corresponding symbolic representation and cannot be empty to distinguish them from missing values. During the blind examination period, statisticians should judge the handling of outliers from both medical and statistical aspects.

Ultrasound images, both static and dynamic, will be collected for possible adjunct and long-term studies. In addition, all the patients will be followed up for 1 month after the intervention.

The volunteers who are responsible for collecting the data have extensive clinical experience, are dedicated to the work, and have received training and guidance. Data will be stored by two independent investigators to ensure reliability and validity.

We will also focus on and collect information from participants who stop or deviate before the intervention is completed. To increase participant retention and enthusiasm, we will establish workflow manuals, contact patients regularly, communicate properly and take effective care of their health.

### Statistical analysis

A predefined statistical analysis plan will be followed. All the statistical analyses will be conducted using IBM SPSS (Statistics 30.0.0). A *p* value of less than 0.05 will indicate statistical significance. Categorical variables will be reported as counts and percentages. Continuous variable data will be presented as mean ± standard deviation for normally distributed data, or median (interquartile range, IQR) for non-normally distributed data.

Analyses will be performed on both the intention-to-treat (ITT) population and the per-protocol (PP) population. The ITT population includes all randomized participants who received at least one dose of the intervention. The PP population includes only participants who completed the study protocol without major protocol violations.

The primary analysis will compare the complete expulsion rate of small gallbladder stones at day 3 post-intervention between the two groups using the chi-square test.

Key secondary analyses will include:

Comparison of complete expulsion rates at day 6 post-intervention between the two groupsWithin-group comparisons of changes in gallbladder volume and gallbladder wall thickness from baseline to day 3 and day 6Comparison of the incidence of adverse events between the two groups

For dichotomous variables, the chi-square test or Fisher’s exact test will be used as appropriate. For continuous variables, the independent samples t-test will be used for normally distributed data, and the Mann–Whitney U test will be used for non-normally distributed data.

After the last patient has completed the 30-day follow-up, a blinded endpoint adjudication committee will independently review all primary and secondary endpoint data.

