### Trial design

This is a parallel-group randomized controlled superiority trial with a 1:1 allocation ratio, not a cross-over design. The control group receives placebo for the first 3 days followed by functional fatty acids for the subsequent 3 days. The primary comparisons are: (1) between the experimental group (3 days of functional fatty acids) and the control group (3 days of placebo) at day 3; and (2) between the experimental group (6 days of functional fatty acids) and the control group (3 days of placebo + 3 days of functional fatty acids) at day 6.

This delayed-intervention design was chosen over a 6-day placebo-controlled design primarily for ethical reasons. Our pilot study demonstrated a 25% complete expulsion rate at day 3 with functional fatty acid treatment, and withholding a potentially effective intervention for the full 6 days would be ethically questionable. Additionally, this design allows us to evaluate both the short-term efficacy of the intervention (day 3 comparison: active treatment vs. placebo) and the effect of treatment duration (day 6 comparison: 6 days of continuous treatment vs. 3 days of delayed treatment). Importantly, the day 6 comparison is not between active treatment and placebo, but between two different durations of active treatment.

The core objective of this superiority design is to demonstrate that oral functional fatty acids (experimental intervention) are significantly more effective than the control intervention in promoting the expulsion of small gallbladder stones. This design was selected on the basis of the research hypothesis of the trial: preliminary evidence from preclinical studies and pilot data suggests that compared with the control intervention, functional fatty acids improve gallbladder motility and better regulate bile composition, thereby facilitating the passage of small stones.

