### Intervention description

Data pertaining to the small gallstones will be extracted from the electronic medical records of outpatients who underwent gallbladder ultrasound examination at this hospital. Follow-ups will be conducted via telephone. If a patient meets the inclusion and exclusion criteria, expresses willingness to participate, and has no clinical symptoms related to gallstones, a gallbladder ultrasound will be repeated by a trained and experienced sonographer. Only patients with gallstones measuring less than 2 mm at this follow-up examination will be eligible for enrollment. Eligible patients will be randomly assigned to the experimental group or the control group. The attending physician will explain the potential risks and benefits of the intervention, and written informed consent will be obtained from all participants.

The patients in the experimental group will take 50 mL of oral functional fatty acids on an empty stomach every morning for 6 consecutive days. In the control group, patients will first receive oral placebos for 3 days, followed by the same dose of oral functional fatty acids as the experimental group for the next 3 days. The blinded ultrasound physicians will perform gallbladder ultrasounds on the 3rd and 6th days after treatment to evaluate the effect of small gallstone expulsion. We chose the 3rd and 6th days after the intervention as the observation time points for evaluating the effect of small gallstone expulsion for the following reasons. On the basis of our experience and data from pilot studies, after 6 days of oral functional fatty acids, small gallstones were effectively expelled or exhibited a reduction in their content. However, it remains unclear whether the small gallstones were expelled precisely on the 6th day of intervention or before. Therefore, using the median value as a reference, we aimed to identify an optimal time point for evaluating the expulsion of small gallstones. Well-trained volunteers will follow up with patients during treatment to increase patient compliance and facilitate timely recording and management of any complications.

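### The single per-protocol set is defined by completing the study protocol, so stopping on days 4–6 removes a finished day-3 result from the day-3 per-protocol comparison (ITT is not affected)

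*Protocol article*

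**What the plan says.** All under Statistical analysis in the protocol article, unless another section is named:

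- **Analysis sets.** "Analyses will be performed on both the intention-to-treat (ITT) population and the per-protocol (PP) population". Neither is named as primary.
- **PP.** "The PP population includes only participants who completed the study protocol without major protocol violations". Completion and absence of major violations are two separate conditions. Neither is tied to an endpoint or a time point, and neither term is defined further.
- **ITT.** "The ITT population includes all randomized participants who received at least one dose of the intervention". There is no completion condition.
- **Primary comparison.** "The primary analysis will compare the complete expulsion rate of small gallbladder stones at day 3 post-intervention between the two groups using the chi-square test".
- **Length of dosing.** Intervention description: the experimental arm takes the product "on an empty stomach every morning for 6 consecutive days". Trial design: "The control group receives placebo for the first 3 days followed by functional fatty acids for the subsequent 3 days".
- **Later follow-up.** Data collection and management: "all the patients will be followed up for 1 month after the intervention". Recruitment gives "the ability to complete the 30-day follow-up" as an example of the eligibility criteria. Neither section links this to PP membership.

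**The concern.** A PP analysis of a day-3 endpoint should ask who followed the assigned regimen up to day 3. This definition asks who finished everything. A control who took three days of placebo, was scanned on day 3 and then stopped on day 5 because of diarrhoea on the oil leaves the placebo side of the day-3 PP comparison, because of an effect of the other product. An experimental participant who was clear at day 3 and stopped on day 5 leaves as well. Neither departed from the regimen that the day-3 comparison tests.

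Two features of this trial make the selection more than a formality. First, on days 4–6 controls meet the oil for the first time while the experimental arm is in its second three days of it, so reasons for stopping need not match. Second, stopping can be tied to the outcome. The section Data monitoring says that a small stone may lodge at the sphincter of Oddi and that the intervention is then discontinued, while complete expulsion is judged from the gallbladder alone. A stone that has left the gallbladder can therefore contribute to a success and also cause the stop.

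Because both sets are analysed and neither is named as primary, the affected PP estimate would stand beside the ITT estimate as support or contradiction.

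**Working it through.** **Inputs from the documents.** Assumed day-3 clearance is 25% (experimental) and 8% (control), from the section on assumed outcome rates. There are 50 participants per arm and 10% total attrition is anticipated, with no timing given (Allowance for participant attrition). No rate of stopping on days 4–6 is stated, so the rates below are assumptions. No figure in the plan rests on the PP definition; the reference value is the planned difference, 25 − 8 = 17.0 points.

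**Step 1. Who is removed.** For a participant with days 1–3 taken, a valid day-3 scan and a stop on day 4, 5 or 6:

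| Set | Condition | Kept for day 3? |
|---|---|---|
| ITT | randomized, at least one dose | yes |
| PP | study protocol completed, no major violation | no, because the 6-day regimen was not completed |

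**Step 2. Effect on the expected PP difference.** Let p be the true day-3 rate in an arm, s the fraction of its clearers who stop on days 4–6, and f the fraction of its non-clearers who stop. The rate in the PP set is

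r = p(1 − s) / [p(1 − s) + (1 − p)(1 − f)]

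| Assumed stopping | Experimental | Control | Difference (points) |
|---|---|---|---|
| none | 25.0% | 8.0% | 17.0 |
| 10% of control non-clearers | 25.0% | 0.08/(0.08 + 0.92×0.9) = 8.8% | 16.2 |
| 20% of control non-clearers | 25.0% | 0.08/(0.08 + 0.92×0.8) = 9.8% | 15.2 |
| 10% of experimental non-clearers | 0.25/(0.25 + 0.75×0.9) = 27.0% | 8.0% | 19.0 |
| 20% of experimental non-clearers | 0.25/(0.25 + 0.75×0.8) = 29.4% | 8.0% | 21.4 |
| 10% of clearers, both arms | 0.225/0.975 = 23.08% | 0.072/0.992 = 7.26% | 15.8 |
| 20% of clearers, both arms | 0.200/0.950 = 21.05% | 0.064/0.984 = 6.50% | 14.5 |

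The differences run from 14.5 to 21.4 points, that is −2.5 to +4.4 around 17.0. These are scenario values, not bounds.

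**Step 3. Effect on the test, by example.** Uncorrected chi-square, X² = N(ad − bc)² / (product of the four margins), with whole counts near the planned rates:

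- No loss, 12/50 vs 4/50: 100×(12×46 − 38×4)²/(50×50×16×84) = 100×400²/3,360,000 = 4.76, p = 0.029. Difference 24.0 − 8.0 = 16.0 points.
- Two experimental clearers lost, 10/48 vs 4/50: 98×(10×46 − 38×4)²/(48×50×14×84) = 98×308²/2,822,400 = 3.29, p = 0.070. Difference 20.8 − 8.0 = 12.8 points.
- Five experimental non-clearers lost, 12/45 vs 4/50: 95×(12×46 − 33×4)²/(45×50×16×79) = 95×420²/2,844,000 = 5.89, p = 0.015. Difference 26.7 − 8.0 = 18.7 points.

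With so few clearers, two exclusions after day 3 can move the PP result across 0.05. In all three examples every participant met the day-3 regimen.

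**The case against.** The strongest reply is that the PP sentence is a conventional one-line summary. The same section refers to a predefined statistical analysis plan, which is not shown. That plan may define completion and major violations and may apply PP by endpoint. This has weight, and it is why the point concerns the wording as it stands and not how the analysis will be run. But the article does state a completion criterion, does not limit it by endpoint, and pairs it with a day-3 primary comparison. An analysis plan that follows the sentence literally would inherit the mismatch.

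Late stopping may also be uncommon. Both arms take the same oil on days 4–6. Pilot compliance was 100% on the 80%-of-dose definition, the only pilot adverse events were two cases of mild diarrhoea that resolved without intervention, and the section Harms lets participants with mild or moderate events continue. No passage says that participants are told their day-3 scan result, so stopping because of that result is conjecture; stopping because of symptoms does not need it. All this limits the likely size, but it does not make the definition fit the endpoint.

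Three stronger readings are tempting and are not supported:

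- *That the day-3 comparison as a whole loses these participants.* It does not. The ITT set has no completion condition and keeps them.
- *That missing the 30-day follow-up removes a participant from PP.* Follow-up is part of the described study, but no passage ties it to PP membership, and the mention in Recruitment concerns ability to attend, judged at enrolment.
- *That each arm could shift by about −8 to +3 points.* This places all 10% attrition after day 3 and makes everyone lost in an arm a clearer at one end and a non-clearer at the other. For controls the upward shift is at most 4/45 − 4/50 = 8.9 − 8.0 = 0.9 points.

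**Conclusion.** The point holds for the PP version of the day-3 comparison only. As worded, the PP set selects on what happens after the primary endpoint has been measured, in a period when the control arm has changed product. The direction of the bias cannot be foreseen, and its expected size is modest. The sizes rest on assumed stopping fractions, because the documents give none, and on the protocol's own 25% and 8%. The examples show that the PP p-value is sensitive to one or two handfuls of such exclusions at most; they do not predict that these will occur. It should be corrected because PP is analysed alongside ITT with neither named as primary, and the correction is simple.

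**What to change.** Replace the single PP definition with endpoint-specific sets:

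- **Day-3 PP set:** eligible, assigned product taken on days 1–3, valid day-3 scan, and no major protocol violation before that scan.
- **Day-6 PP set:** the corresponding criteria up to the day-6 scan.
- **General rule:** events after an endpoint's scan, including stopping on days 4–6 (for day 3) or missed later follow-up, do not remove a participant from that endpoint's PP set. This also settles the unclear status of the 30-day contact.

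The cost is a sentence or two in the analysis-set definition, written before unblinding, with ethics committee approval as the protocol requires for changes to analyses. No new data are needed, since the protocol already plans to collect information on participants who stop or deviate early. Treatment and visits do not change, and the day-3 PP set can only stay the same size or grow relative to the present wording.

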### Secondary objectives

In this study, relevant indices, including the volume of the gallbladder and the thickness of the gallbladder wall, will be compared among patients via ultrasound examinations before and after the intervention. The purpose of this study is to determine whether the intervention affects gallbladder contraction function and can alleviate gallbladder inflammation.

Moreover, we will compare the rates of clinical adverse events, such as abdominal pain and diarrhea, before and after the intervention. This comprehensive comparison will help us gain a more in-depth understanding of the impacts and safety implications of the dietary therapy studied in this trial.

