#### Standardized ultrasound assessment protocol

All ultrasound examinations will be performed using a Philips EPIQ 7 ultrasound system with a 3–5 MHz convex array probe, following a standardized protocol. Patients will be examined in the supine and left lateral decubitus positions after an 8-h fast.

*Image evaluation*: All images will be independently reviewed by two board-certified sonographers with ≥10 years of experience in abdominal ultrasound, who are blinded to group assignments and previous examination results.*Disagreement resolution*: Any discrepancies between the two reviewers will be resolved by a third senior sonographer, whose decision will be final.*Image storage*: Both static images (at least 2 images per examination, including longitudinal and transverse views of the gallbladder) and dynamic video clips (5–10 s per view) will be stored in a secure digital repository for future review and quality control.

Measurement standardization:

*Gallstone number*: Counted in multiple views to ensure all stones are identified*Maximum stone diameter*: Measured in three orthogonal planes, with the largest value recorded*Gallstone volume*: Calculated using the ellipsoid formula: Volume = (*π*/6) × length × width × depth*Gallbladder volume*: Calculated using the ellipsoid formula: Volume = 0.52 × length × width × depth*Gallbladder wall thickness*: Measured at the anterior wall of the gallbladder in the longitudinal view, avoiding the neck and fundus regions

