#### Secondary outcome measures

Table 1 presents detailed information on the secondary outcome measurements. These data demonstrate the effectiveness and safety of the intervention process, as well as the potential risks.

**Table 1 tab2:** Secondary outcome measures.

Secondary outcome measure	Assessment time point	Operational definition
Gallbladder volume	7 days post-intervention	Measured by abdominal ultrasound using the ellipsoid formula: Volume = Length × Width × Depth × 0.52
Gallbladder wall thickness	7 days post-intervention	Measured by abdominal ultrasound at the thickest point, accurate to 0.1 mm
Serum total bilirubin	7 days post-intervention	Determined by standard laboratory assay; normal reference range: 3.4–17.1 μmol/L
Post-intervention abdominal pain	7 days post-intervention	Assessed using the Numerical Rating Scale (NRS)^1^; scores range from 0 (no pain) to 10 (worst imaginable pain)
Post-intervention acute pancreatitis	14 days post-intervention	Defined as the presence of characteristic abdominal pain plus serum amylase level ≥3 times the upper limit of normal^2^
Post-intervention gastrointestinal bleeding	14 days post-intervention	Defined as melena (black tarry stools) or a decrease in hemoglobin (Hb) level ≥20 g/L from baseline^3^
Post-intervention nausea, vomiting, and diarrhea	14 days post-intervention	Recorded as the daily frequency of each symptom during the 14-day follow-up period

^1^NRS: Numerical rating scale. A validated self-report pain assessment tool.

^2^Upper limit of normal for serum amylase at our institution: 100 U/L.

^3^Normal reference range for hemoglobin at our institution: 120–160 g/L (female), 130–175 g/L (male).

^4^All ultrasound examinations will be performed by two independent blinded sonographers with ≥10 years of experience in abdominal imaging. All laboratory tests will be conducted using standard methods at the Clinical Laboratory of the First Hospital of Lanzhou University.

Participant timeline please see Figure 2.

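### For gallbladder volume and wall thickness, the only listed contrast is within-group although the aim is causal, and Table 1 conflicts on timing and wall site

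*Protocol article*

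**What the plan says.** All references are to the protocol article.

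- **Aim.** Secondary objectives says that gallbladder volume and wall thickness "will be compared among patients via ultrasound examinations before and after the intervention", in order to "determine whether the intervention affects gallbladder contraction function and can alleviate gallbladder inflammation".
- **Listed analysis.** Under the key secondary analyses, Statistical analysis gives one item for these outcomes. It is labelled within-group: "comparisons of changes in gallbladder volume and gallbladder wall thickness from baseline to day 3" and day 6. The other two items in that list, day-6 expulsion and adverse events, are each worded as comparisons of the two arms.
- **Tests.** "For continuous variables, the independent samples t-test will be used for normally distributed data". When normality fails, the section turns to the Mann–Whitney test, which is likewise for independent samples. No paired test is named.
- **Times.** Table 1 (Secondary outcome measures) puts both outcomes at "7 days post-intervention" and at no other time. Intervention description schedules the ultrasounds on days 3 and 6.
- **Wall site.** Standardized ultrasound assessment protocol: "Measured at the anterior wall of the gallbladder in the longitudinal view, avoiding the neck and fundus regions". Table 1: "Measured by abdominal ultrasound at the thickest point, accurate to 0.1 mm".
- **Exposure.** Under Trial design, controls take placebo on days 1–3 and the active product on days 4–6. The same section acknowledges that day 6 compares a longer with a shorter exposure.

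**The concern.** The aim is causal, but the listed contrast is before against after within each arm. Such a change mixes any effect of the product with time trend, repeat-scan effects and regression to the mean. Patients are selected on stone size rather than on volume or wall thickness, so regression to the mean may be modest, but the other sources remain. In the control arm, the change from baseline to day 6 also mixes three days of placebo with three days of active product.

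The randomized placebo comparison at day 3 separates these influences from the effect of the product, and it is not listed for these two outcomes. The likely substitute is to report that one arm changed significantly and the other did not, which is not a test of a difference between arms.

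Table 1 adds to the problem. Its single time falls after both arms have had the active product, and its wall-site wording does not match the ultrasound protocol. Gallbladder volume matters here because gallbladder contraction is the mechanism that the Background and Discussion propose.

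**Working it through.** The protocol gives no standard deviation, effect size or power for these outcomes, so there is no stated figure to reproduce. The check is a comparison of the text, followed by illustrations whose assumptions are stated.

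**Text side by side**

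| Item | One place | Another place | Result |
|---|---|---|---|
| Contrast | Secondary objectives: effect of the intervention | Statistical analysis: within-group change only | Aim and listed contrast do not match |
| Test | Statistical analysis: independent-samples tests | Same section: within-group item | Named tests fit an unlisted contrast and not the listed one |
| Time | Intervention description and Statistical analysis: days 3 and 6 | Table 1: 7 days only | Conflict; Table 1 omits day 3 |
| Wall site | Ultrasound protocol: anterior wall, not neck or fundus | Table 1: thickest point | Wording not reconciled |
| Volume formula | Ultrasound protocol: 0.52 × L × W × D | Table 1: the same | Agrees |

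Whether 7 days is counted from the start or the end of dosing, it falls after day 6. By then the control arm has taken the active product.

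**Significance in one arm only, with no treatment effect.** Let both arms have the same true change and let each within-arm test have power p. Then P(exactly one arm significant) = 2p(1 − p).
- p = 0.05: 2 × 0.05 × 0.95 = 0.095
- p = 0.20: 2 × 0.20 × 0.80 = 0.32
- p = 0.50: 2 × 0.50 × 0.50 = 0.50

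**If an independent-samples test were used on before/after data.** Assume equal variances and a within-patient correlation ρ. The standard error is too large by a factor √(1/(1 − ρ)), and the actual two-sided type I error is 2[1 − Φ(1.96/√(1 − ρ))].
- ρ = 0.3: factor √(1/0.7) = 1.20, type I error 0.019
- ρ = 0.5: factor √(1/0.5) = 1.41, type I error 0.006
- ρ = 0.7: factor √(1/0.3) = 1.83, type I error 0.0003

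With n = 50, ρ = 0.5 and a true within-arm shift of 0.4 SD, power (normal approximation) is 0.52, against 0.81 for a paired test. The error is therefore conservative: it costs power and does not create false positives.

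**Gain from baseline adjustment between arms.** Per-patient variances, with common variance σ²:
- day-3 value alone: σ²
- change from baseline: 2σ²(1 − ρ)
- ANCOVA: σ²(1 − ρ²)

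Ratio of ANCOVA to change = (1 − ρ²)/[2(1 − ρ)] = (1 + ρ)/2. At ρ = 0.5 this is 0.75 and at ρ = 0.8 it is 0.90, a reduction of 25% and 10%.

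Ratio of ANCOVA to day-3 value alone = 1 − ρ². At ρ = 0.5 this is 0.75 and at ρ = 0.8 it is 0.36, a reduction of 25% and 64%.

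**The case against.** The best defence is that the sentence on tests for continuous variables is a general rule. It stands next to the chi-square/Fisher sentence and reads naturally as covering comparisons between arms. The list of key secondary analyses says what will be included and does not claim to be complete. A separate analysis plan is mentioned, and it may name paired tests or add the between-arm comparison.

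Much of this stands, and it rules out three stronger readings:

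- A reader might infer that the plan applies an independent-samples test to paired data. The text never makes that link, so the standard-error and type I figures above are conditional illustrations. The absence of a named paired test could be settled in the analysis plan.
- A reader might infer that these outcomes cannot show a treatment effect at all. They can: both arms are scanned at day 3 and baseline values are collected. Only the listed contrast fails to use them.
- A reader might infer that the two wall-site descriptions are different measurements, or that sites will be mixed between scans. The thickest point of the anterior wall, away from neck and fundus, would satisfy both texts, and nothing says that different scans will use different sites.

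Figure 2, the assessment schedule, is not shown and may include a day-7 scan. Table 1 and Statistical analysis would still disagree on which times count.

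The defence does not reach the choice that is printed. The within-group label sits between two items expressly worded as between arms, the stated aim is causal, and Table 1 leaves out day 3. An unseen analysis plan could add to this text but would not remove its contradictions.

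**Conclusion.** The point holds in this form: the only contrast listed for gallbladder volume and wall thickness does not use the randomized control, although the aim is to learn what the intervention does. The named tests match a comparison that is not listed for these outcomes. The assessment times conflict, and the wall-site wording is not reconciled.

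The size cannot be derived from the protocol. At an assumed correlation of 0.5 to 0.8, ANCOVA lowers variance by about 10–25% relative to a between-group comparison of change, and by 25–64% relative to day-3 values alone. The larger range has the weaker comparator. The main gain is validity, because either between-group analysis uses the randomization. ANCOVA is the more efficient of the two.

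These are secondary outcomes and the primary endpoint is unaffected. The change should be made, but the trial's main conclusion does not depend on it.

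**What to change.** - In Statistical analysis, make the between-group difference at day 3, adjusted for the baseline value by ANCOVA, the main analysis of gallbladder volume and wall thickness, with a rank-based version if the data are clearly skewed.
- Fit the same model at day 6 and label it a comparison of durations.
- Report within-group changes descriptively, with paired methods, and do not base claims of effect on them.
- Reconcile the assessment times across Intervention description, Table 1 and Statistical analysis, keeping day 3 as an analysed time. If a day-7 scan is intended, say what it is for.
- Reconcile the wall-site definition between the ultrasound protocol and Table 1, so that one definition applies to every scan.

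The cost is wording, plus the ethics-committee approval that the protocol requires for changes to outcomes or analyses. Baseline measurements and day-3 scans in both arms are already planned, so no further data are needed.
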